## Methods

### Study design and ethics

This prospective randomized controlled study will be used to evaluate the effects of TRE in overweight and obese women with PCOS. After signing the informed consent form, participants will be randomly divided into two groups for a 1-week baseline survey, a 12-week intervention, and a 6-month follow-up. Recruitment for the study began on July 20, 2024, and will end by June 20, 2025. Participants will provide written informed consent. This study was conducted in accordance with the Declaration of Helsinki, and approved by the Medical Ethics Committee of the University of South China (Number: NHHL027), and registered in the Chinese Clinical Trial Registry (ChiCTR 2400086815). If protocol changes are required, the study leader will communicate with ethics Committee members and trial registry staff.

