### Setting

The setting for this study encompasses the First Affiliated Hospital of University of South China. Study procedures will be conducted within the outpatient departments of gynecology and nutrition, as well as at the participants’ homes. To avoid interaction between the two groups of participants, the study measurements for the TRE group will be conducted exclusively at their homes. Recruitment will be conducted via flyers, posters, phone calls, social media, and emails.

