### Randomization and blinding

In this study, randomization will be achieved using opaque closed envelopes and simple random sampling. Based on sample size estimates, two groups will be allocated to a 1:1 ratio. To ensure an unpredictable distribution, 96 random numbers (either 0 or 1, each making up half) will be generated. These numbers will be written on 96 cards and sealed in yellow-brown envelopes for concealed grouping. After unsealing, participants will be assigned to either the “control group” (0) or the “TRE group” (1) based on the random number on the card. Generating the assignment order, recruiting participants, and assigning participants to the intervention will be performed separately by different researchers in this research group.

This study will be an open-label clinical trial design, and participants cannot be blinded because the intervention plan will limit the time of participant eating. To reduce bias error, blinding of outcome assessors and data analysts will be used to compensate. To achieve this, outcome assessors will undergo training to ensure they conduct evaluations in a standardized and objective manner, free from any influence stemming from knowledge of the participant’s group assignment. Additionally, data analysts will work with anonymized datasets, where all identifying information related to group assignment has been removed. Furthermore, stringent protocols will be enforced to prevent any unauthorized communication among outcome assessors, data analysts, and those responsible for assigning participants to groups or delivering interventions.

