### Procedures and measures

#### Baseline investigation and development of calorie restriction program

Before the formal trial begins, all potential participants will undergo a 1-week baseline survey. Baseline surveys are designed to confirm participants’ eligibility for the study, assess their interest in the study, and obtain informed consent. At the same time, a series of baseline measures will be taken, such as weight, BMI, body composition, sex hormones, glucose and lipid metabolism indicators, as well as quality of life assessment, sleep quality assessment, anxiety and depression assessment. In addition, a weekly dietary assessment will be conducted using food journals and food photographs to record in detail the participants’ daily eating patterns, food intake and calorie intake. Work intensity and basal metabolic rate will be assessed using the International Physical Activity Questionnaire and a basal metabolic meter, respectively. Based on these assessments, the daily calorie requirements for each participant will be calculated. In the personalized calorie restriction program, each participant will be required not to exceed their individual daily calorie needs and will have the autonomy to decide the types and quantities of food they consume, while ensuring that the overall calorie goal is met.

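### The protocol contradicts itself on whether randomisation comes before or after the 1-week baseline survey that confirms eligibility and sets the calorie limit

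*Protocol article*

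**What the plan says.** Study design and ethics gives the sequence in one sentence: "After signing the informed consent form, participants will be randomly divided into two groups for a 1-week baseline survey", followed by the 12-week intervention and the follow-up. This is the only sentence that explicitly places randomisation relative to the survey, and it places it first.

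The section on the baseline investigation and the calorie restriction program describes the same week differently: "Before the formal trial begins, all potential participants will undergo a 1-week baseline survey". It gives the purpose as follows: "Baseline surveys are designed to confirm participants’ eligibility for the study, assess their interest in the study, and obtain informed consent". The week also supplies the baseline values ("At the same time, a series of baseline measures will be taken, such as weight, BMI, body composition, sex hormones", then metabolic indicators and questionnaires) and the individual calorie limit ("Based on these assessments, the daily calorie requirements for each participant will be calculated"). The Control group and TRE group sections apply that limit in both arms.

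Randomization and blinding describes 96 sealed envelopes, half for each arm, but does not say at what point an envelope is opened. It also states: "This study will be an open-label clinical trial design, and participants cannot be blinded". Data analysis commits to analysing every randomised participant in her assigned group.

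**The concern.** Baseline should be fixed before anyone can know the allocation. Under Measures, outcomes are assessed as changes from baseline, so a baseline influenced by knowledge of the arm carries into every change score. The calorie limit is part of the regimen in both arms. If its inputs are reported with the arm known, the limits could differ between arms for reasons unrelated to need, and the effect of the eating window would be mixed with that of the calorie limit.

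Eligibility is the second issue. If it is confirmed only after allocation, a woman who fails it has already used one of the fixed assignments, and neither way of handling her is clean. Recruitment began in July 2024 according to Study design and ethics, so the order may already have governed real allocations.

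**Working it through.** **Step 1. Compare the two descriptions.**

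| Item | Study design and ethics | Baseline investigation section |
|---|---|---|
| Consent | before randomisation and survey | obtained as part of the survey |
| Who enters the survey | participants already divided into two groups | all potential participants |
| Eligibility | not placed | confirmed by the survey |
| Randomisation | after consent, before the survey | not placed, but implied after the survey |

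**Step 2. Can both hold?** The reference to the formal trial could mean the start of the intervention, and that phrase alone would allow randomisation first. The rest does not fit. Women already allocated are no longer only potential participants, and consent cannot both precede allocation and be a product of a survey that follows it. Confirming eligibility in that week would mean confirming it after allocation. The descriptions therefore conflict.

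**Step 3. What follows if randomisation comes first.**

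- *Baseline data.* Participants are unblinded. Food diaries and photographs, the physical activity questionnaire, the sleep index, SF-36 and HADS would be completed with the arm known. Scanner weight, hormone assays and metered basal metabolic rate are less open to reporting effects, although a woman who knows her arm may start to change how she eats.
- *Calorie requirement.* It is calculated from that week's assessments, which include self-reported intake and activity.
- *Assessors.* Blinding is planned: "To reduce bias error, blinding of outcome assessors and data analysts will be used to compensate". Under Setting, however, "the study measurements for the TRE group will be conducted exclusively at their homes". If allocation precedes baseline and this rule covers baseline measurements, the place of measurement would reveal the arm from the start.
- *Assignments.* An ineligible woman already holds one of 48 assignments in her arm.

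**Step 4. Power, as an illustration only.** Inputs from Sample size: σ = 3.87, δ = 2.5 kg, Z values 1.96 and 0.84, dropout 20% to 25%.

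The plan's own figure: 2 × (1.96 + 0.84)² × 3.87² / 2.5² = 37.57, rounded up to 38 per group. 38 / 0.80 = 47.5, rounded up to 48, which matches the plan. At 25% dropout, 38 / 0.75 = 50.7, so 51 would be needed.

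The document gives no ineligibility rate. Take e = 5%, 10% or 15% as assumptions, with dropout d, and suppose the ineligible women are excluded:

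n = 48 × (1 − e) × (1 − d); power = Φ(2.5 / (3.87 × √(2/n)) − 1.96)

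| e | n, d = 20% | Power | n, d = 25% | Power |
|---|---|---|---|---|
| 0 | 38.4 | 0.808 | 36.0 | 0.783 |
| 5% | 36.5 | 0.788 | 34.2 | 0.762 |
| 10% | 34.6 | 0.766 | 32.4 | 0.739 |
| 15% | 32.6 | 0.742 | 30.6 | 0.715 |

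The loss due to ineligibility is the difference from the e = 0 row in the same column: 2.0, 4.2 and 6.6 points at 20% dropout, and 2.1, 4.4 and 6.8 points at 25%.

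**The case against.** The strongest reply is that Study design and ethics offers only a summary sentence, while the baseline section is the operative procedure and implies the sound order. Fig 1, the SPIRIT schedule, is not shown in the text at hand and may settle the matter. This stands in part: it cannot be concluded that the trial randomises first. It does not remove the contradiction, because a site following the summary sentence as written would open envelopes too early, and the randomisation section does not correct it.

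A reader might infer more than the document supports in four ways.

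- *That baseline data are in fact collected with allocation known.* This is conditional on the order in Study design and ethics being followed.
- *That all staff know the arm.* Participants would know. Assessors are meant to be blinded and kept apart from those who allocate or deliver the intervention. Home-only measurement threatens this but does not prove it has failed.
- *That the intention-to-treat commitment is broken.* No section says randomised women found ineligible are dropped. Termination criteria does not list ineligibility, and Data analysis keeps everyone randomised. The document leaves a dilemma but does not state a violation.
- *That ineligibility explains the whole fall from 80% power to the mid-70s.* Dropout of 25% alone already gives about 78%. Many criteria, such as age, BMI, pregnancy and surgical history, could also be checked before the survey week, so the number found ineligible during it may be small.

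**Conclusion.** The point holds as an internal contradiction about the order of consent, baseline survey and randomisation. The harm is conditional. If randomisation precedes the survey, self-reported baseline data and the inputs to the calorie requirement are recorded with the participant's arm known, and ineligible women take up fixed assignments with no clean way to analyse them. The document gives no basis for estimating the size or direction of any resulting bias.

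Power is a side issue. The cost is roughly 2 to 7 percentage points beyond dropout. That figure rests on an assumed 5% to 15% ineligibility and on excluding those women, which the stated intention-to-treat rule would not do. The case for acting is that analysis cannot reliably remove a bias introduced at baseline, while settling the order costs almost nothing.

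**What to change.** State one order in Study design and ethics, in Randomization and blinding and in the baseline investigation section, and check that Fig 1 agrees:

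1. written informed consent;
2. the 1-week baseline survey;
3. eligibility confirmed;
4. baseline values and the calculated calorie requirement recorded;
5. the next envelope opened.

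Reword the summary sentence in Study design and ethics accordingly. Place consent before the survey in the baseline section. Add to Randomization and blinding that no envelope is opened until steps 1 to 4 are documented.

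If anyone has already been randomised before her baseline survey, keep her in the intention-to-treat set in her assigned arm, flag her by the dates of allocation and baseline, and repeat the primary comparison without the flagged participants as a sensitivity analysis.

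The cost is a few sentences in the protocol, an amendment notified to the ethics committee and the registry, and an instruction to the site. The sample size stays at 48 per group, and no visits or measurements are added.

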### Setting

The setting for this study encompasses the First Affiliated Hospital of University of South China. Study procedures will be conducted within the outpatient departments of gynecology and nutrition, as well as at the participants’ homes. To avoid interaction between the two groups of participants, the study measurements for the TRE group will be conducted exclusively at their homes. Recruitment will be conducted via flyers, posters, phone calls, social media, and emails.

### Participants

#### Sample size

The study will enroll 96 overweight and obese women with PCOS, and the sample size is based on the estimation formula for the sample size required to compare the two sample means of the measurement data [13]:

$$N=\frac{2*{\left(Z_{1-\frac{\alpha }{2}}+Z_{1-\beta }\right)}^{2}*\sigma^{2}}{\delta^{2}}$$

N represents the sample size for each group. $Z_{1-\frac{\alpha }{2}}$ is the Z-score corresponding to the desired significance level (α). For a significance level of 0.05, $Z_{1-\frac{\alpha }{2}}$ = 1.96. $Z_{1-\beta }$ is the Z-score corresponding to the desired power (1 - β). For a power of 80%, $Z_{1-\beta }$ = 0.84. According to the reviewed literature [39], σ = 3.87, δ = 2.5kg. Considering a 20% to 25% dropout rate, the final sample size will be determined to be 48 participants per group, for a total of 96 participants.

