**Methods:**

This randomized controlled trial will enroll 96 overweight and obese women with polycystic ovary syndrome (PCOS), who will be randomly assigned to either a TRE group (with an eating window from 8:00 a.m. to 16:00 p.m.) or a control group (without eating time restrictions), with 49 participants in each group. Evaluators and data analysts will remain blinded to group allocation throughout the study. The primary outcomes, including changes in weight and body mass index (BMI), will be assessed weekly. Secondary outcomes, encompassing alterations in sex hormones, metabolic parameters, body composition, sleep quality, quality of life, anxiety, and depression, will be evaluated monthly. Compliance and safety will be continuously monitored throughout the study. Additionally, a 6-month follow-up will be conducted at the end of the trial to assess the long-term effects of TRE. Statistical analysis will include the Anderson-Darling test for normality, T-test/Wilcoxon test based on distribution, mixed-effects models for assessing time/group effects, Cox model for time-to-event analysis, repeated ANOVA for change analysis, and sensitivity analysis. All tests will be conducted using appropriate software, with a significance level set at P<0.05. Missing data will be imputed.

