All statistical analyses will be performed using appropriate software (e.g., GraphPad Prism 8.0.1 or R, depending on the specific requirements of the analysis), and bilateral tests will be used for all results. Statistical significance will be determined at the P < 0.05 level. The intention-to-treat (ITT) population approach will be adopted to handle program non-adherence, ensuring that all randomized participants are included in the analysis according to their original group assignment. Missing data will be addressed using appropriate imputation methods, such as multiple imputation, to minimize bias and maintain the integrity of the statistical analysis.

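### The abstract's 49 per group contradicts the total of 96, and 48 per group covers 20% dropout at 80% power but not the full stated range up to 25%

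*Protocol article*

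**What the plan says.** The Sample size section of the protocol article uses the normal-approximation formula for comparing two means. Its inputs are a 0.05 significance level (Z = 1.96), 80% power (Z = 0.84) and "σ = 3.87, δ = 2.5kg". It does not print the number that the formula returns. It goes straight to the enrolment figure: "Considering a 20% to 25% dropout rate, the final sample size will be determined to be 48 participants per group", 96 in total.

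Randomization and blinding is consistent with this: "two groups will be allocated to a 1:1 ratio", and "96 random numbers (either 0 or 1, each making up half) will be generated", which fixes 48 cards per arm.

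The Methods paragraph of the abstract also gives a total of 96, but the same sentence continues "with 49 participants in each group".

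Data analysis confirms two-sided testing ("bilateral tests will be used for all results"). It also specifies an intention-to-treat population with imputation of missing data.

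**The concern.** Arm size is a basic design figure, and the abstract is the part most widely read. If 49 per group stands there, an arm of 48 in the results could be taken for a recruitment shortfall when it is the plan.

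The dropout sentence has a different problem. It offers one enrolment number as the answer for a range of dropout rates. A given number needed for analysis leads to different enrolment figures at 20% and at 25%, so 48 cannot be the 80% power answer at both ends. A reader who takes the sentence at face value would believe that the design holds 80% power even if a quarter of the women are lost.

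**Working it through.** **Inputs.** All are from the Sample size section unless noted: Z = 1.96 for alpha 0.05, two-sided (Data analysis); Z = 0.84 for 80% power; σ = 3.87; δ = 2.5 kg; dropout 20% to 25%; 1:1 allocation (Randomization and blinding).

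**1. Evaluable number per group, by the article's formula.**

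N = 2 × (1.96 + 0.84)² × 3.87² / 2.5² = 2 × 7.84 × 14.9769 / 6.25 = 37.57, rounded up to 38.

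**2. Allowance for dropout, N / (1 − d).**

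- At 20%: 38 / 0.80 = 47.5, rounded up to 48. This reproduces the stated figure.
- At 25%: 38 / 0.75 = 50.7, rounded up to 51 (102 in total). Starting from the unrounded value, 37.57 / 0.75 = 50.1, which also rounds up to 51.

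**3. Largest dropout that 48 per group can absorb at 80% power.**

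1 − 37.57 / 48 = 0.217, or about 21.7%.

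**4. Power with 48 enrolled per group**, by the same normal approximation: power ≈ Φ(δ / (σ√(2/n)) − 1.96), with n the completers per group.

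| Dropout | Completers per group | Power |
|---|---|---|
| 20% | 38.4 | 80.8% |
| 21% | 37.92 | 80.3% |
| 22% | 37.44 | 79.8% |
| 23% | 36.96 | 79.3% |
| 24% | 36.48 | 78.8% |
| 25% | 36 | 78.3% |

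The last row in full: 3.87 × √(2/36) = 0.912; 2.5 / 0.912 = 2.741; 2.741 − 1.96 = 0.781; Φ(0.781) = 0.783. The largest shortfall is 80 − 78.3 = 1.7 percentage points. The difference detectable with 80% power at 36 per group is 2.8 × 0.912 = 2.55 kg, against the planned 2.5 kg.

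**5. The abstract's arm size.**

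2 × 49 = 98, not 96. From the cards, 96 / 2 = 48 per arm. Nor would 49 per group resolve the dropout question: 49 × 0.75 = 36.75 completers, with power 79.1%.

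**The case against.** The best defence on power is that the calculation is right at the lower end of its range. The correct inflation at 20% gives exactly 48, and at the upper end little is lost. The detectable difference moves by 0.05 kg. A true SD of √(36 × 2.5² / (2 × 2.8²)) = 3.79 instead of 3.87, about 2% smaller, would close the gap, and an SD taken from the literature is unlikely to be known that precisely. All of this stands, and it is why the point is minor.

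The power figures also treat each dropout as contributing nothing. The article plans an intention-to-treat analysis with imputation, and Table 1 has weight measured weekly, so women who leave early may still contribute data. That stands too: the completers-only figure is an approximation, and the article gives no basis for quantifying what would be recovered. But the Sample size section itself plans by a dropout allowance, so its claim is fairly checked on that footing.

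Four stronger readings are tempting and are not supported:

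- *The design misses 80% power throughout the stated range.* It does not. By the stated formula, power is at or above 80% from 20% to about 21.7% dropout.
- *The wrong inflation was used.* Multiplying, 38 × 1.25 = 47.5, also rounds up to 48, so a reader might infer that step. The article does not show its inflation step, and the correct division at 20% gives the same 48. Nothing shows that multiplication was used.
- *Even 20% dropout falls short.* A noncentral t calculation gives 79.4% with 38 per group. That is the ordinary gap between the t-test and the normal approximation that the article declares. It is not an error in the stated figure.
- *There are two rival enrolment totals.* Every explicit total is 96, and the allocation cards are unambiguous. Only the abstract's per-group number disagrees.

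**Conclusion.** Two corrections are warranted, both minor.

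The abstract's 49 per group is an internal contradiction that no reading reconciles. The text that governs allocation consistently gives 48 per group, so conduct and analysis do not depend on the slip.

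The Sample size section claims slightly more than its figures deliver. At 80% power, 48 per group covers 20% dropout, and up to about 21.7%, but not 25%, which would need 51 per group. At 25% dropout, power is about 78%. This rests on the article's own σ, δ and normal-approximation formula, on equal dropout in both arms, and on counting completers only.

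**What to change.** 1. In the abstract, change the per-group figure from 49 to 48.
2. Keep 96 in total. In the Sample size section, replace the dropout range with a statement of what the number achieves. For example: the formula gives 38 evaluable women per group; 48 per group (38 / 0.80, rounded up) allows for 20% dropout at 80% power; if dropout reaches 25%, leaving 36 per group, power is about 78%.

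The cost is wording only. The number of participants, the allocation and the analysis stay as they are. The one concession is a slightly less favourable power statement at the upper end of the dropout range.

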#### Inclusion criteria

(1) age 18–49 years old; (2) a diagnosis of PCOS according to the Rotterdam criteria [40]; (3) BMI ≥ 24 kg/m^2^ (where BMI between 24–27.9kg/m^2^ is overweight, BMI > 28kg/m^2^ is obese); (4) willing to sign a consent form.

#### Exclusion criteria

(1) the participant has used weight loss drugs or hormone therapy in the past six months; (2) body weight fluctuation > 5% in the past three months; (3) on pregnancy, breastfeeding, preparation for pregnancy or perimenopausal period; (4) regular high-intensity exercise or night shifts due to work; (5) serious heart disease or stroke (including myocardial infarction, unstable angina, heart bypass surgery, PTCA, congestive heart failure, and ischemic heart disease) within six months; (6) participants with other diseases (such as primary amenorrhea, thyroid dysfunction, malignant tumors, diabetes, severe gastrointestinal, renal or liver diseases); (7) history of hypotension; (8) participants who have undergone bariatric surgery or have been diagnosed with cancer.

